#### Implementation—aims #1–5

2.5.2

Quantitative data will be analyzed using a descriptive approach (e.g., counts, means, recruitment and screen-positive/negative rates, and visit attendance). This will be complemented by qualitative feedback focused on acceptability and feasibility of the research protocol.

Qualitative data will be coded by experienced research staff, supervised by experts with knowledge of the FCU® and qualitative and mixed methods. Videotaped sessions, speech samples, focus group, and interview data will be transcribed verbatim, with all transcribed and open-ended survey data collectively imported into and managed using the Lumivero (2023) *NVivo* (Version 14) www.lumivero.com platform. The research team will then apply codebook-based, thematic analysis to qualitative data sources; the codebook will be informed *a priori* by our EPIS and FCU® Implementation Frameworks, but also allow for the iterative generation of new codes and thematic domains, as data collection, analysis, and interpretation unfold (84, 85). Peer-debriefing with experts in qualitative research, the FCU®, parenting practices, and ASD will support validity of codes and determination coding sufficiency. Use of multiple coders, consensus coding approaches, interim member-checking, and thick description will ensure the integrity and reliability of our analysis.

## Ethics and dissemination

3

The study protocol follows SPIRIT guidelines and was approved by the Hamilton Integrated Research Ethics Board (HIREB, #14475, March 2023, Version 6.0) and registered at clinicaltrials.gov (NCT05280613).

### Informed consent

3.1

A copy of the informed consent form will be provided to the family at the screening visit (either emailed or given in person) for review and discussion prior to the baseline visit. Informed consent will be obtained by trained research staff from caregivers and children who are capable of consenting, before conduct of any study-specific procedures and after the study has been thoroughly described and all questions answered. Assent will be obtained from children who are capable of assenting. Understanding of the study will be confirmed by asking clarifying questions, e.g., “Why are we doing this study? What are some of the good/bad things that might happen in this study? Who will know what you say during the study? Do you have to take part in the study?

### Adverse events

3.2

Adverse events (AEs) are any untoward health outcome that occurs during study participation, regardless of whether the event can be attributed to study participation. Since the FCU® is a psychological and behavioral intervention, this study involves minimal risk. Therefore, AEs will not be systematically elicited at each study contact; however if caregivers report an AE to a clinician or research staff person, it will be reported to the Research Coordinator and documented according to local Research Ethics Board guidelines. Anticipated AEs that are considered to signal unresolved risk to caregiver, child, research staff, or clinician (e.g., severe aggression or depression, suicidality) will be discussed with the PI. Child protection, police, or emergency medical service will be alerted if there is concern about imminent risk to life of an adult or safety of a child. The LPI or designated back-up person will determine if other steps must be taken to mitigate risk to caregiver, child, research staff, or clinician.

### Risk mitigation

3.3

As the psychosocial intervention under study is considered low-risk, and delivered within a hospital-based clinical setting where clinical supervisors routinely assess safety and risk, a Data Safety and Monitoring Board (DSMB) was not assembled. Clinical concerns for both intervention and TAU participants are reviewed with a panel of clinicians and investigators and administrative leaders as issues arise. Stoppage rules were not deemed necessary for the purposes of this study.

Research staff and clinicians will be trained to evaluate and address concerns about serious or imminent mental health risk in caregivers, child safety assessments, and reporting duties, as well as crisis services available in the community. They will immediately apprise the LPI (or back-up) of concerns about child safety or serious parental mental health issues noted during study visits. Safety concerns will also be discussed at weekly team meetings supervised by a qualified psychologist and/or psychiatrist. In case of mental health or safety emergencies, the LPI or designated back-up will assess the participant and make appropriate safety and/or reporting decisions as guided by their clinical expertise and professional duties to report. All actions taken to mitigate risk and outcomes of these actions will be documented on a Risk Mitigation Report Form. If the LPI determines that a participating caregiver must be withdrawn from the study for any reason, the investigator will notify the caregivers and inform them of other available options for services in the community and, if consent is provided, notify their family physician or other health care provider of the decision. Research staff and FCU® clinicians also receive training to mitigate risk related to working with children and families. Injuries or threats to staff will be documented and discussed at weekly FCU® meetings (if occurring in FCU® intervention participants) as well as research team meetings.

### Confidentiality, data management, and access

3.4

As part of the informed consent process, caregivers will be informed about privacy and confidentiality of data, and also about the potential need to breach confidentiality if there are concerns about any child’s safety or imminent harm to any adult necessitating advising appropriate authorities. No data will be released to third parties without the explicit written consent of the participant or their legal guardian.

Each participant will be assigned a sequential identification number and these numbers, rather than names, will be used to collect, store, and report participant data throughout the study. The study team will keep a separate log of identifiable participant information for internal tracking purposes; this log will be kept separately from data and will always be securely stored and accessible only to research staff. Research study source documents will be kept securely in password-protected files on secure McMaster servers, or in locked storage at the Offord Centre for Child Studies. Paper and electronic data will be stored securely for a minimum of 7 years after final study report or primary peer review publications. All staff will be PHIPPA trained.

Source documents are defined as original documents, data, and records. They may include hospital records, clinical and/or office charts, clinical notes or evaluation checklists, videotaped observations, and communication records (e.g., telephone logs, emails). Study staff will clearly define the various source documents used to support the study as part of their local data management processes. Data collection will be completed by authorized study site personnel designated by the LPI. Participants will not be identified in the study database by name or initials; they will be identified by their unique participant ID.

Survey data will be collected on password-protected laptops and tablets and de-identified at the point of collection. Where possible, questionnaire data will be collected in electronic format using Qualtrics, an Application Service Provider (ASP) using a Software-as-a-Service (SaaS) platform for creating and distributing online surveys and other research services. Qualtrics uses Transport Layer Security (TLS) encryption for all transmitted internet data. Its services are hosted by trusted third party data centers that are audited using the industry standard SSAE-16 SOC 1 Type 2 method. All data are stored within the region where data are collected and will not be moved from that region.

### Data processing and data management

3.5

Data will be checked for valid values and ranges, between item logical consistency, and within-participant variation. Participants will be included in the data analysis provided they complete all screening and baseline procedures, and that there is at least some post-baseline data available. All study-related source data will be entered into the study database. Only FCU® intervention data listed as study-relevant variables will be directly entered into the database (e.g., outcomes, covariates, mediators, moderators, and exploratory variables). If items are left blank when these measures are completed, the standard procedure as outlined in the manual for each questionnaire will be followed to account for missing data. Site staff will ensure that the study records for all participants are up to date as soon as possible soon after participant completion of study, with field and form exceptions reviewed and accepted to account for all required data.

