#### Randomization and blinding

2.1.5

Randomization will occur following the baseline visit to reduce risk of differential attrition. Participants will be randomly assigned to one of two conditions (FCU® or Treatment as Usual) using an internet-based randomization service; https://www.randomize.net/. Randomization will be stratified by child chronological age (6–10 and 11–17 years) and by presence/absence of co-occurring intellectual disability. Participants will be informed of their treatment arm status by the Research Coordinator or another research staff member who will not conduct any follow-up measures.

Participants will be informed of their right to withdraw from the study at any time. Furthermore, the lead principal investigator (LPI) may decide to withdraw a participating family from the study, if required, to mitigate undue risk to caregiver, child, research staff, or FCU® clinician.

Study participants will be withdrawn from the study under the following conditions:

If it is determined that the caregiver or child has an acute psychiatric crisis (e.g., psychosis) that will interfere with the ability to participate in the study.If a caregiver is experiencing an extreme crisis (e.g., related to an abusive or violent relationship) that interferes with the ability to participate in the study.If caregiver, child, research staff, or FCU® clinician experience an adverse event that is deemed by the LPI be an unacceptable safety risk.Death of child or participating caregiver.If participant behaviors or circumstances are deemed to unduly compromise the safety of the treating clinician or research staff (e.g., violence or unsafe behaviors toward research staff or clinician; unsafe conditions in home).If the LPI deems it is in the participants’ best interest to discontinue the study treatment.Loss of custodial caregiver status, if consent not obtained from replacing custodial caregiver (e.g., other caregiver, child protection service).

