#### 3-month assessment (30 min)

2.3.3

This is a brief visit that involves an interview and questionnaires to measure primary and secondary outcomes. It can take place in the family’s home, clinic, a community location, or over the phone with questionnaire completion through emailed links.

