#### Effectiveness—aim #1

2.5.1

Analyses will be conducted following an intent-to-treat approach. Two-wave latent difference score models will be used to evaluate whether participation in the FCU®, compared to TAU, is associated with greater decreases in child EBP (primary outcome) and caregiver depression and parenting stress from baseline to 6 and 12 months post-baseline, and greater increases in positive parenting from baseline to 6 and 12 months post-baseline. A sensitivity power analysis indicates that an *N* = 80 is powered to detect a significant regression coefficient equivalent to Cohen’s *d* = 0.56, α ≤ 0.05 (one-tailed), which is aligned with systematic reviews noting moderate (~*d* = 0.60) effect sizes for parenting programs among caregivers of autistic children (19, 20). A one-tailed test was chosen based on our directional hypotheses and the wealth of evidence supporting the effectiveness of the FCU®. Given that *d* = 0.56 is somewhat larger than that found in previous studies of the FCU® in non-autistic children, we will also conduct two additional sets of analyses. First, we will calculate a Bayes Factor for each analysis to determine whether the pattern of effects are more consistent with the null (the two groups do not differ) or alternative hypotheses (the two groups differ). Second, we will conduct exploratory, descriptive analyses to determine the percentage of participants in each condition defined *a priori* as responders using the ABC and CGI, and describe intervention-, organization and policy-relevant child, family and intervention characteristics in each group.

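### The stated intent-to-treat principle conflicts with the article's own rules, which can remove randomised families, or their outcomes, because of events after randomisation

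*Protocol article*

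**What the plan says.** Section 2.5.1 (Effectiveness, aim #1) sets the principle: "Analyses will be conducted following an intent-to-treat approach". The model follows: "Two-wave latent difference score models will be used to evaluate whether participation in the FCU®, compared to TAU", for change from baseline to 6 and 12 months.

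Section 3.5 (Data processing and data management) sets the analysis set. Participants are "included in the data analysis provided they complete all screening and baseline procedures, and that there is at least some post-baseline data available".

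Section 2.1.5 (Randomization and blinding) fixes the timing: "Randomization will occur following the baseline visit to reduce risk of differential attrition". The same section lists mandatory withdrawals, introduced by "Study participants will be withdrawn from the study under the following conditions". The seven grounds include acute psychiatric crisis, extreme caregiver crisis, an adverse event judged an unacceptable safety risk, and behaviours or circumstances that "are deemed to unduly compromise the safety of the treating clinician or research staff". A further ground is the lead investigator's view that it is in the participants' "best interest to discontinue the study treatment".

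Section 2.3.3 describes the first post-baseline assessment, at 3 months: "This is a brief visit that involves an interview and questionnaires to measure primary and secondary outcomes". It may be done by phone with emailed questionnaire links.

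**The concern.** Intent-to-treat means that every randomised family is analysed in its assigned arm. A rule that admits a family only if follow-up data exist selects on something that happens after randomisation, and can therefore depend on the arm. The article states both the principle and the rule and does not reconcile them.

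The withdrawal list matters because it can create the missing data that section 3.5 then acts on. It treats stopping the intervention as a reason to leave the study. Its grounds (crisis, unsafe behaviour, adverse events) are plausibly related to child irritability and caregiver depression, which are trial outcomes.

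At stake is whether the 6-month comparison is protected by randomisation. The test is one-tailed at 5%, so any bias towards FCU goes straight into the false-positive rate.

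**Working it through.** **1. The rules side by side.**
- Screening and baseline procedures are complete before randomisation (2.1.5). The exit for developmental age below 2 is also tied to the baseline visit (2.4.2.3). This half of the section 3.5 condition cannot depend on the arm and is not at issue.
- The other half, some post-baseline data, is settled only after randomisation. It is the half that conflicts with 2.5.1.
- Section 2.1.5 removes families from the study; it does not say that they leave the analysis. A family withdrawn before the 3-month assessment has no post-baseline data and is excluded under 3.5. A family withdrawn after 3 months still satisfies 3.5 but loses its 6- or 12-month outcome, unless collection continues, which the article does not state.

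**2. The plan's own figure.** Inputs: N = 80, one-tailed alpha 0.05, d = 0.56 (2.5.1). Assumed because not stated: 1:1 allocation (40 per arm) and 80% power.
- Normal approximation: d = (1.645 + 0.842) × sqrt(2/40) = 0.556.
- Noncentral t: minimum detectable d = 0.561; power at 0.56 is 0.799.

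The stated 0.56 reproduces. It uses all 80 families and allows for no exclusions. If 5%, 10% or 15% of each arm is lost, power at d = 0.56 falls to 0.78, 0.76 or 0.74.

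**3. Illustration of bias.** The documents give no exclusion rate, so every input here is an assumption. There is no true effect, a share f of FCU families is removed, those families average m SD worse than their whole arm, and none are removed from TAU. The retained FCU mean shifts by

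bias = f × m / (1 − f).

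The one-tailed error is the probability that a noncentral t exceeds its 5% critical value, with n1 = 40(1 − f), n2 = 40 and noncentrality bias × sqrt(n1 × n2 / (n1 + n2)).

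| FCU removed | m (SD) | bias (SD) | one-tailed error |
|---|---|---|---|
| 2 of 40 | 0.5 | 0.05 × 0.5 / 0.95 = 0.026 | 0.063 |
| 2 of 40 | 1.0 | 0.05 × 1.0 / 0.95 = 0.053 | 0.079 |
| 4 of 40 | 0.5 | 0.10 × 0.5 / 0.90 = 0.056 | 0.080 |
| 4 of 40 | 1.0 | 0.10 × 1.0 / 0.90 = 0.111 | 0.122 |
| 6 of 40 | 0.5 | 0.15 × 0.5 / 0.85 = 0.088 | 0.102 |
| 6 of 40 | 1.0 | 0.15 × 1.0 / 0.85 = 0.176 | 0.185 |

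Equal numbers of equally ill families removed from both arms give zero bias.

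**4. Effect of using baseline.** The table is for an unadjusted difference in follow-up scores, while the plan models change. If removal depends on the follow-up score and the baseline to follow-up correlation is r (assumed 0.3 to 0.7), the bias is multiplied by about (1 − r) for a change score and (1 − r²) for a baseline-adjusted comparison. For the largest row, 0.176 becomes 0.176 × 0.7 = 0.12 down to 0.176 × 0.3 = 0.05 for change, and 0.176 × 0.91 = 0.16 down to 0.176 × 0.51 = 0.09 with adjustment. These are in SDs of the follow-up score.

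**The case against.** The strongest reply is that this is mostly a matter of label. Requiring some post-baseline data is a familiar modified intent-to-treat set. Section 2.1.5 governs conduct and is not an analysis rule. The trial is described as proof-of-principle and aims at preliminary estimates. The estimator, missing-data handling and sensitivity analyses usually sit in an analysis plan that is not shown. Much of this stands, and it limits the point. It does not remove the conflict, because the article itself fixes an inclusion rule that differs from the principle it states.

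A reader might infer that families doing badly will leave the FCU arm more readily. The documents do not show this. Most withdrawal grounds apply to both arms, section 3.3 says that clinical concerns are reviewed for intervention and TAU participants alike, and weekly to biweekly contact arises only for families who take the optional EDP sessions. TAU families, who are offered the FCU only after study completion, might leave more often. What stands is that stopping study treatment can in practice arise only in the FCU arm, and that this arm has more clinician contact. Section 3.2 does not elicit adverse events systematically, so more contact gives more occasions to hear of one. Unequal loss is therefore possible, with its direction open.

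A reader might also infer that the requirement to complete baseline procedures breaks intent-to-treat. It does not, because it is settled before allocation.

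Finally, analysing everyone by likelihood does not by itself cure outcome-dependent loss. In a simulation with 15% of FCU and 5% of TAU removed, 1 SD worse, and a correlation of 0.3 to 0.7, the likelihood estimate from all randomised families kept a bias of 0.09 to 0.06 SD, against 0.09 to 0.05 SD for baseline-adjusted analysis of those retained. This objection is correct, and it is why redefining the analysis set is only part of the fix.

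**Conclusion.** The contradiction holds and rests on the text alone: 2.5.1 states intent-to-treat, 3.5 conditions inclusion on a post-randomisation event, and 2.1.5 ties stopping treatment to leaving the study with no statement that outcomes continue. This should be fixed before analysis.

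The consequence is a possible bias, not a demonstrated one. The illustrated 0.03 to 0.18 SD, set against the planned 0.56, and the 6% to 19% one-tailed error rest on assumed removal counts, an assumed 0.5 to 1 SD deficit, loss from FCU only, 40 per arm and no baseline adjustment. They show scale and are not an estimate for this trial. The stated N = 80 and d = 0.56 are unaffected.

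**What to change.** 1. **Section 3.5:** define the primary analysis set as all randomised families in their assigned arm, using all available scores. If the post-baseline-data condition is kept, call the set modified intent-to-treat in 2.5.1.
2. **Section 2.1.5:** leave the stopping criteria as they are, but separate stopping FCU sessions from stopping outcome collection. State that caregiver questionnaires continue after sessions stop where consent and circumstances permit; emailed links are already allowed at 3 months.
3. **Section 2.5.1 or the analysis plan:** add one sensitivity analysis for outcome-dependent missing data, for example making the missing FCU outcomes progressively worse until the conclusion changes. If the analysis plan already has one, a cross-reference is enough.

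The cost is protocol and consent wording, some additional emailed questionnaires and one extra analysis. The sample size does not change.

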### Dissemination

3.6

We will integrate implementation and effectiveness findings into renewed quality improvement and adaptation of the FCU® model. Should the proof-of-principle effectiveness study fail to demonstrate significant intervention effects, we will integrate qualitative and quantitative findings to enhance the model and/or target population and re-evaluate within a larger RCT or pre/post study. We will publish findings in academic journals; clinical, family, and academic conferences and presentations.

## Conclusion

4

Everyday relationships, activities, and interactions, including positive parenting and cohesive family relationships, represent key mental health protective factors throughout the development of autistic children. Such protective factors are themselves shaped by the broader social determinants of child and family health, including household income security and social supports. Autistic children and youth who experience co-occurring EBP are more likely to experience psychosocial adversity, such as caregiver depression, income stress, and social isolation. These risk factors can compound negative effects by acting as barriers for families seeking to access autism services, parenting support, and mental healthcare. While positive parenting approaches have demonstrated robust and reliable effects on child EBP in families of autistic children, there is a paucity of intervention approaches that effectively address the developmental, mental health, and psychosocial complexity present in the daily lives of many autistic children and their families.

The study was designed as a response to research that suggests that treatment will have greatest chance of success if it: (a) provides a comprehensive assessment of the social-ecological influences on child and family, (b) effectively engages and supports caregivers dealing with greater life complexity and psychosocial strain, (c) efficiently tailors family-centered care plans, and (d) targets positive parenting practice as a path to shaping child self-regulation. Furthermore, research-to-practice gaps often mean long lags and low uptake of evidence-based interventions into regular clinical care. Hybrid implementation-evaluation approaches seek to shorten this gap by evaluating the effectiveness of interventions within real-world settings while simultaneously describing barriers and facilitators related to program uptake, sustained delivery and scale-up.

In the current study, we will evaluate the FCU®, an assessment-driven ecologically sensitive model of family-centered care aimed at preventing and/or decreasing EBP in children and supporting positive parenting and family well-being in children at high risk of persistent EBP, within a “real-world” autism service setting. The study has several strengths with respect to intervention and study design: Several features of the FCU® enhance its fit for families and children experiencing developmental, mental health, and psychosocial complexity, including a strength-based focus, positive parenting lens, motivational approach, and an emphasis on tailoring intervention to diverse child and family needs. The study design includes both caregiver report, blinded independent evaluator-led interviews, and observational measures. The mixed methods RCT design will enable a more comprehensive and nuanced understanding of caregivers’ experience of the program and processes of change aimed at explaining varied patterns of response (and non-response) to intervention and will enable qualitative comparison and triangulation of data between participating caregivers and FCU® providers. Finally our team is composed of clinicians, administrators and researchers, which has facilitated delivery of the RCT within an established autism service setting with commitments to sustain and/or adapt delivery of the model for further research or quality improvement as needed. By embedding the study in a real-world setting, we hope to create a more efficient research-to-practice pathway.

We anticipate encountering limitations in the study, particularly in relation to trade-offs inherent in more pragmatic designs. First, our research question investigates whether intervention participation in the FCU® confers advantages to autistic children and youth referred for care within an established clinical setting. Because this question is of interest to administrators and clinicians, we elected to include a broad sample of clients/patients with respect to age and cognitive and spoken language ability. Second, differential response to caregiver-led intervention may occur based on child or caregiver characteristics (e.g., child co-occurring ID) however our sample size is not powered to detect moderator effects. We will provide preliminary descriptive estimates of effect sizes by child age and ID status as stratification factors. Finally, using an effectiveness, rather than efficacy, design, we did not validate diagnoses with gold standard tests such as the Autism Diagnostic Interview-Revised (ADI-R) (86) and/or Autism Diagnostic Observational Schedule (ADOS-2) (87). It is possible that some clients will be referred to an autism service whose profile is best understood by other diagnoses than autism, however this compromise was made to facilitate clinical flow and assess the added value of the FCU® to clinic clients “as is.” Using the SCQ-C (67), we will explore whether autistic symptom severity is associated with indices of response to intervention.

Scalable, ecologically focused family-centered interventions offer promise as key components of a public health framework aimed at reducing mental health inequities among autistic children and youth, and their caregivers. Results from this study will inform further adaptations and evaluation efforts aimed at “making the race fair” for autistic children and youth and their families.

